### 9.5.6 Hepatic Monitoring

If a subject experiences elevated alanine aminotransferase (ALT)  $\geq 3 \times$  upper limit of normal (ULN), alkaline phosphatase (ALP)  $\geq 2 \times$  ULN, or elevated total bilirubin (TBL)  $\geq 2 \times$  ULN, liver tests will be performed to confirm the abnormality. Additional safety data may be collected if required, as defined in the protocol. Where applicable, the following will be presented.

The subjects' liver disease history and associated person liver disease history data will be listed. Any concomitant medication that have potential for hepatotoxicity, including acetaminophen will be listed. Results from any hepatic monitoring procedures, such as a magnetic resonance elastography (MRE) scan, and biopsy assessments will be listed, if performed.

Hepatic risk factor assessment data will be listed. Liver related signs and symptoms data will be summarized by treatment, and listed. Alcohol and recreational drug use data will also be listed.

All hepatic chemistry, hematology, coagulation, and serology data will be listed. Values outside the reference ranges will be flagged on the individual subject data listings.

### 9.5.7 Immunogenicity Assessments

The frequency and percentage of subjects with pre-existing antidrug antibody (ADA) and with treatment-emergent ADAs (TE ADA) to LY3475766 will be tabulated and listed.

For subjects who are ADA negative at baseline, TE ADAs (treatment induced) are defined as those with a titer 2-fold (1 dilution) greater than the minimum required dilution of the assay (1:10). For subjects who are ADA positive at baseline, TE ADAs (treatment boosted) are defined as those with a 4-fold (2 dilution) increase in titer compared to baseline. The frequency and percentage of subjects with cross-reactive and neutralizing antibodies, if measured, may also be tabulated for subjects with TE ADA.

### 9.5.8 Injection-Site Reactions

Injection-site reaction AE data will be listed and summarized by treatment in frequency tables (if appropriate).

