## 7. Treatment

### 7.1. Treatment Administered

The doses to be administered are presented in Section 5.1 and Table GZEA.5.

The investigational product will be administered either via an SC injection or as a slow IV infusion (over at least 30 minutes for Cohorts 1 and 2, or at least 60 minutes for Cohort 6). For SC administration, LY3475766 and placebo will be administered at a maximum volume of 2 mL per injection. A maximum of 6 injections may be necessary to achieve higher planned dose levels.

The drug product LY3475766 is supplied for clinical trial use as 75 mg of a lyophilized powder in a glass vial. Further dilution may be needed for IV administration. See Pharmacy Instructions for more information.

Placebo will be sterile saline (0.9% NaCl). Placebo doses should be held in the pharmacy for an equivalent amount of time as is required to prepare doses of LY3475766.

Investigative sites must have resuscitation equipment, emergency drugs, and appropriately trained staff available during the injection or infusion and for at least 6 hours after subjects have completed receiving their injections or infusions.

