**Table GZEA.5. Treatments Administered Subcutaneously**

| Dose Level   | LY
Concentration
per Vial
(mg/mL) | Number of Vials | Volume
per
Injection
(mL) | Number of Injections | Total
Volume of
Injection
(mL) |
|--------------|--------------------------------------------|-----------------|------------------------------------|----------------------|-----------------------------------------|
| LY 100 mg/PL | 50                                         | 1.3             | 2.0                                | 1                    | 2                                       |
| LY 300 mg/PL | 50                                         | 5               | 2.0                                | 3                    | 6                                       |
| LY 600 mg/PL | 50                                         | 10              | 2.0                                | 6                    | 12                                      |

Abbreviations: LY = LY3475766; PL = placebo.

Injection site selected for SC administration should be the abdominal region approximately 5 cm from the umbilicus and the treatment has to be administered through the needle applied at approximately 45° with pinching of the skin. Because subjects may receive multiple injections per dose, each injection should be administered in a different abdominal quadrant in Cohorts 3 and 4 (rotating from right upper quadrant, to right lower quadrant, to left lower quadrant, to left upper quadrant), the quadrant used should be recorded at the time of the injection. For Cohort 5 where 6 SC injections are necessary, the injections should be administered into 6 separate regions of the abdomen: upper right, middle right (same level as umbilicus), lower right, lower left, middle left (same level as umbilicus), and upper left. Administering in a clockwise or counterclockwise direction should be considered to avoid injecting into the same location twice. The abdominal location for each injection should be recorded at the time of the injection. All injections should be performed within a total of 10 minutes. Subcutaneous administration of

LY3475766 should be done by a limited number of individuals for consistency. The same type of syringe and needle should be used for all subjects to ensure all injections are delivered to a consistent depth target into the SC space.

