#### **9.4.5. Injection-Site Assessments (for Subcutaneous Doses Only)**

If an AE of injection-site reaction (ISR) is reported by SC dosing cohorts, a form will be triggered in the eCRF to capture specific information about this reaction (for example, erythema, induration, categorical pain, pruritus, edema). If there is more than 1 symptom of an ISR that meets the definition of an AE (for instance erythema and pruritus), a single AE of ISR will be recorded on the AE page of the eCRF.

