### Figure GZEA.1. Dose escalation for Protocol J1T-MC-GZEA.

This is a randomized double-blinded SAD design in dyslipidemic but otherwise healthy male and female subjects, investigating the safety, tolerability, PD, and PK of LY3475766 versus placebo.

Subjects will be enrolled in 6 cohorts:

- Cohort 1: 10 mg LY3475766 or placebo IV
- Cohort 2: 30 mg LY3475766 or placebo IV
- Cohort 3: 100 mg LY3475766 or placebo SC
- Cohort 4: 300 mg LY3475766 or placebo SC
- Cohort 5: 600 mg LY3475766 or placebo SC
- Cohort 6: 1000 mg LY3475766 or placebo IV

Doses and the number of cohorts may be adjusted based on ongoing review of the PK, safety, and tolerability data.

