## 6. TREATMENTS

The following is a list of the study treatment names that will be used in the TFLs.

| Study Treatment Name | Treatment order in TFL |
|----------------------|------------------------|
| Placebo              | 1                      |
| 10 mg LY3475766 IV   | 2                      |
| 30 mg LY3475766 IV   | 3                      |
| 100 mg LY3475766 SC  | 4                      |
| 300 mg LY3475766 SC  | 5                      |
| 600 mg LY3475766 SC  | 6                      |
| 1000 mg LY3475766 IV | 7                      |

Placebo data will be pooled. The above dose levels will be updated on the TFLs for the actual dose received.

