## **9.5 Safety and Tolerability Assessments**

### **9.5.1 Adverse events**

Where changes in severity are recorded in the Case Report Form (CRF), each separate severity of the adverse event (AE) will be reported in the listings, only the most severe will be used in the summary tables. A pre-existing condition is defined as an AE that starts before the subject has provided written informed consent and is ongoing at consent. A non-treatment emergent AE is defined as an AE which starts after informed consent but prior to dosing. A treatment-emergent AE is defined as an AE which occurs postdose or which is present prior to dosing and becomes more severe postdose.

All AEs will be listed. Treatment-emergent AEs will be summarized by treatment, severity and relationship to the study drug. The frequency (the number of AEs, the number of subjects experiencing an AE and the percentage of subjects experiencing an AE) of treatment-emergent AEs will be summarized by treatment, Medical Dictionary for Regulatory Activities (MedDRA) version 22.0 system organ class and preferred term. The summary and frequency AE tables will be presented for all causalities and those considered related to the study drug. Any serious AEs will be listed.

Discontinuations due to AEs will be listed.

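### The injection-site reaction table compares SC doses given as 1, 3 or 6 injections with one all-cohort placebo pool that is not matched on injection count and is about half IV

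*Combined protocol and SAP*

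**What the plan says.** SAP section 9.5.8 gives the whole ISR plan in one sentence: "Injection-site reaction AE data will be listed and summarized by treatment in frequency tables (if appropriate". SAP section 6 lists the treatment groups for the tables. There is one placebo entry, and the rule is "Placebo data will be pooled". SAP section 9.5.1 shows what an AE frequency table holds: "the number of AEs, the number of subjects experiencing an AE and the percentage of subjects experiencing an AE".

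The protocol matches placebo to active on injection exposure within each SC cohort. Section 7.1 states that "LY3475766 and placebo will be administered at a maximum volume of 2 mL per injection". Table GZEA.5 gives each dose level and its placebo the same count: 1 injection at 100 mg, 3 at 300 mg and 6 at 600 mg, each of 2 mL. The text under the table confirms the largest count: "For Cohort 5 where 6 SC injections are necessary, the injections should be administered into 6 separate regions of the abdomen". That text also requires the abdominal location of each injection to be recorded.

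Cohorts 1, 2 and 6 are intravenous, for example "Cohort 6: 1000 mg LY3475766 or placebo IV". Their placebo subjects receive no SC injection but belong to the same pooled group. No text in either document splits placebo by route, cohort or number of injections for the ISR summary.

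**The concern.** A subject given six injections has six opportunities for a local reaction, a subject given one has one, and an IV subject has none. The design controls for this within each cohort, because placebo subjects receive as many injections as the active subjects beside them. Pooling placebo over all cohorts discards that control for the one safety outcome that depends most directly on it.

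The primary objective covers safety and tolerability of single SC as well as IV doses. Local tolerability is part of that, and Protocol section 5.4 says that the data will help identify a dose range for later studies. In the planned table, a product no more irritating than saline would be expected to show an ISR rate that rises with dose and exceeds placebo at 300 and 600 mg. A real drug or dose effect could not be separated from injection count.

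**Working it through.** **Inputs from the documents**
- Concentration 50 mg/mL and 2 mL per injection (Protocol section 7.1 and Table GZEA.5).
- Evaluable subjects: 36 active and 12 placebo, 48 in total (SAP section 7). Allocation is 3:1 (Protocol section 7.2). There are six cohorts: 1, 2 and 6 IV; 3, 4 and 5 SC.

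**Assumptions**
- Equal cohort sizes.
- A per-injection ISR risk p that is the same for drug and saline. The documents give none, so a range is shown.
- Independent injections within a subject (relaxed in step 5).

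**Step 1. Reproduce the plan's figures.** Injections = dose / 50 / 2: 100 mg gives 1, 300 mg gives 3 and 600 mg gives 6, as in Table GZEA.5. Subjects: 36 + 12 = 48; 36/12 = 3; 48/6 = 8 per cohort, that is 6 active and 2 placebo.

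**Step 2. Injections in the comparator.** SC placebo subjects receive 2×1 + 2×3 + 2×6 = 20 injections. Over the 12 pooled placebo subjects the mean is 20/12 = 1.67. Over the 6 SC placebo subjects it is 20/6 = 3.33. Neither equals 1, 3 or 6.

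**Step 3. Expected per-subject rate with no drug effect.** With k injections, P(at least one ISR) = 1 − (1 − p)^k. SC-only placebo is the mean over k = 1, 3 and 6. The SAP's pool is half of that, because 6 of its 12 subjects have k = 0. At p = 5%: 1 − 0.95 = 0.050; 1 − 0.95³ = 0.143; 1 − 0.95⁶ = 0.265; SC-only mean 0.153; SAP pool 0.076.

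| p | 100 mg | 300 mg | 600 mg | SAP pool | SC-only placebo | 600 mg minus SAP pool | 600 mg minus SC-only |
|---|---|---|---|---|---|---|---|
| 2% | 2.0% | 5.9% | 11.4% | 3.2% | 6.4% | +8.2 | +5.0 |
| 5% | 5.0% | 14.3% | 26.5% | 7.6% | 15.3% | +18.9 | +11.2 |
| 10% | 10.0% | 27.1% | 46.9% | 14.0% | 28.0% | +32.9 | +18.9 |
| 20% | 20.0% | 48.8% | 73.8% | 23.8% | 47.5% | +50.0 | +26.3 |

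Over p from 1% to 30%, the ratio of 600 mg to the SAP pool is 2.9 to 3.6; to SC-only placebo it is 1.4 to 1.8. Against the SAP pool, 300 mg is also higher (+6.6 points at p = 5%, +13.1 at 10%) and 100 mg is slightly lower (−2.6 and −4.0).

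**Step 4. Matched comparison.** With placebo shown by cohort, k is the same on both sides, so the expected difference with no drug effect is 0 at every SC dose.

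**Step 5. Correlation.** At the opposite extreme, a subject reacts with probability q whatever the number of injections. SC-only placebo then has rate q, and the excess at 600 mg against it is 0. The SAP pool has rate 6q/12 = q/2, so every SC dose is still expected to show twice the placebo rate.

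**Step 6. Chance.** Under independence, with 6 subjects at 600 mg, the probability that the observed 600 mg rate exceeds placebo at p = 2, 5, 10 and 20% is 50, 76, 90 and 98% against the SAP pool (n = 12). Against SC-only placebo (n = 6) it is 39, 55, 66 and 76%.

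**Step 7. Cohort 4 repeat.** Protocol Appendix 6 says Cohort 4 is to be repeated. If that brings the 3-injection placebo subjects to 4, the rates at p = 10% become 27.8% (SC-only) and 15.9% (SAP pool), so the conclusion does not change.

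**The case against.** The best defence is that nothing inferential rests on this table. ISRs are not a named endpoint; they fall under AE incidence. The summary is descriptive and made only if appropriate, and the study is not powered for hypothesis testing. Individual ISRs are listed, so a careful reader could rebuild the matched comparison. The table shells are a separate document that was not available here and may already separate SC placebo. All of this stands and limits the severity, but a descriptive table with a built-in imbalance still misleads, and the SAP text does not correct it.

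A second defence is that six injections are what a 600 mg SC administration requires, so per-subject incidence after six injections is that administration's actual tolerability. This also stands. It is a reason to keep per-subject incidence rather than replace it with a per-injection rate. It does not justify the unmatched placebo column.

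A reader might infer three stronger things that the documents do not support:
- **That a false dose signal is certain.** It is an expectation that needs a non-zero per-injection risk and, for the SC-only residual, incomplete correlation within subjects. Steps 5 and 6 show how far either could weaken it.
- **That a true effect at 100 mg would be heavily masked.** At p = 10% the shortfall against SC-only placebo is 18 points (10.0% against 28.0%), with a comparator averaging over three times as many injections. The SAP's pool averages only 1.67 injections, and the shortfall against it is about 4 points.
- **That the eCRF loses the reacting site.** Protocol section 9.4.5 says "a single AE of ISR will be recorded on the AE page of the eCRF", but this applies where one ISR has more than one symptom. It does not address reactions at several sites. The listed form contents are examples, so the absence of a location field cannot be established.

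**Conclusion.** The point holds as a mismatch between design and summary. The cohort matching on injection count in Table GZEA.5 is lost in SAP sections 6 and 9.5.8, and nothing else in the documents restores it. With no drug effect and independent injections, the expected excess at 600 mg over the planned comparator is about 19 points at p = 5% and 33 points at p = 10%. IV placebo subjects in the denominator account for part of this. Removing them, which is the obvious repair, leaves about 11 and 19 points from injection count alone.

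These sizes rest on an assumed per-injection risk, on 2 placebo subjects per cohort and on independence. The dilution by IV placebo does not need independence; the SC-only residual does need correlation to be incomplete. Because the table is descriptive and the listings allow partial recovery, this is a cheap improvement to a summary that serves the primary objective. It does not threaten the study's conclusions as a whole.

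**What to change.** In SAP section 9.5.8 and the matching table shell:
- Restrict the ISR table to SC-dosed subjects.
- Show SC placebo by cohort (1, 3 or 6 injections) beside the matching active dose, and also pooled over SC cohorts.
- Label every column with the number of injections per subject.
- Keep per-subject incidence. Where the reacting location can be identified from the data collected, add reactive injections divided by injections given as a supplementary descriptive row.

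The cost is SAP wording and table layout, with no extra visits, samples or subjects. A new eCRF field is not proposed, because it could not prospectively cover SC subjects already dosed by amendment (d).

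The downside is small numbers: about 2 placebo subjects per SC cohort, possibly more at 300 mg after the Cohort 4 repeat. In the per-injection row, 12 of the 20 SC placebo injections would come from the two Cohort 5 placebo subjects, and injections are clustered within subjects. The comparison should therefore stay descriptive.

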## **7.2. Method of Treatment Assignment**

Subjects who meet all criteria for enrollment will be randomized to 1 of the study treatment groups on Day 1. Subjects will be randomized in a 3:1 ratio to receive LY3475766 or placebo.

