## 7. SAMPLE SIZE JUSTIFICATION

Up to 70 subjects may be enrolled so that 48 subjects (LY3475766: 36, Placebo: 12) have sufficient evaluable data.

The sample size is customary for Phase 1 studies evaluating safety and PK, and is not powered on the basis of statistical hypothesis testing.

Subjects who are randomized and who are discontinued from the study (providing that discontinuation was not as a result of a safety finding) may be replaced to ensure that enough subjects complete the study.

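### Injection-site reactions are to be summarised by treatment against one placebo group pooled over IV and SC, so the placebo percentage is understated whenever a placebo reaction occurs

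*Combined protocol and SAP*

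**What the plan says.** SAP 9.5.8 is one sentence: "Injection-site reaction AE data will be listed and summarized by treatment in frequency tables". A closing parenthesis makes the tables conditional on their being appropriate. The section names no population and no denominator.

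The treatments are those in SAP Section 6. Its list has one placebo entry and six active entries, each active entry being a single dose by a single route. Under the list it says "Placebo data will be pooled", with no exception by route or by type of event.

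SAP Section 8 defines the Safety population as every enrolled subject who was dosed, IV or SC. SAP 9.5.1 reports adverse event frequencies by treatment as numbers of events and as numbers and percentages of subjects.

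The protocol collects ISR data by route. Section 9.4.5 is headed as applying to subcutaneous doses only, and says "If an AE of injection-site reaction (ISR) is reported by SC dosing cohorts, a form will be triggered". The reaction is also recorded as an adverse event on the ordinary AE page. SAP Section 5 places SC dosing in Cohorts 3, 4 and 5 (for example "Cohort 5: 600 mg LY3475766 or placebo SC") and IV dosing in Cohorts 1, 2 and 6.

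**The concern.** A placebo subject in Cohort 1, 2 or 6 receives an infusion and has no SC injection site. Under the SAP's rules that subject adds one to the placebo denominator for ISRs and can never add to the numerator. The active columns have no such mixture, because they are already separated by route. The distortion therefore runs one way: the placebo percentage falls and the apparent excess for every SC dose rises.

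Incidence of adverse events is a primary endpoint, and the primary objective covers tolerability of SC doses. Table GZEA.5 gives placebo subjects the same injections as the active subjects in their cohort: 1, 3 or 6 injections of 2 mL. SC placebo is thus the group that shows how much local reaction comes from the injection procedure. Combining it with infused subjects weakens that use.

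**Working it through.** **Inputs**
- Planned evaluable subjects: "Up to 70 subjects may be enrolled so that 48 subjects (LY3475766: 36, Placebo: 12) have sufficient evaluable data" (SAP Section 7).
- Allocation: "Subjects will be randomized in a 3:1 ratio to receive LY3475766 or placebo" (Protocol 7.2).
- Cohorts: "Subjects will be enrolled in 6 cohorts" (SAP Section 5), three SC and three IV.
- Repeat of Cohort 4: Protocol Appendix 6, overview of Amendment (d). The size of the repeat is not given.

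**Reproducing the plan's figure**
48 × 3/4 = 36 active and 48 × 1/4 = 12 placebo, as stated.

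**Split of placebo by route**
The documents do not give cohort sizes. Assuming equal cohorts, 48/6 = 8 per cohort, that is 6 active and 2 placebo. SC placebo = 3 × 2 = 6; IV placebo = 3 × 2 = 6; pooled = 12.

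**Dilution factor**
If x placebo subjects have an ISR, the pooled column prints x/(n_SC + n_IV), while the rate among injected subjects is x/n_SC. Their ratio is f = n_SC/(n_SC + n_IV), whatever x is, provided x > 0.

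| Scenario | SC placebo | IV placebo | f |
|---|---|---|---|
| Planned 48 | 6 | 6 | 6/12 = 0.50 |
| Cohort 4 repeated in full (assumed 8 more, 2 on placebo) | 8 | 6 | 8/14 = 0.57 |
| 70 dosed: Cohort 4 repeat plus 14 others spread evenly by route | 9.75 | 7.75 | 9.75/17.5 = 0.56 |
| 70 dosed: all 22 extra subjects SC | 11.5 | 6 | 11.5/17.5 = 0.66 |
| 70 dosed: all 22 extra subjects IV | 6 | 11.5 | 6/17.5 = 0.34 |

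The last three rows use expected placebo numbers at 3:1 (22/4 = 5.5; 14/4 = 3.5, or 1.75 per route). The last two rows are outer bounds, not forecasts.

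**What would be printed**
The counts below are illustrative, because the documents state no ISR rate.

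| Placebo subjects with an ISR | Pooled, n = 12 | SC only, n = 6 | Pooled, n = 14 | SC only, n = 8 |
|---|---|---|---|---|
| 0 | 0% | 0% | 0% | 0% |
| 1 | 8.3% | 16.7% | 7.1% | 12.5% |
| 2 | 16.7% | 33.3% | 14.3% | 25.0% |
| 3 | 25.0% | 50.0% | 21.4% | 37.5% |

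If an SC dose had the same ISR rate p as SC placebo, the table would show an excess of p × (1 − f). With one placebo ISR this is 16.7 − 8.3 = 8.4 points from the rounded percentages (exactly 1/12, or 8.3 points) in the planned design, and 12.5 − 7.1 = 5.4 points with Cohort 4 repeated.

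**The case against.** The strongest objection is that the denominator is inferred. SAP 9.5.8 states none, the detailed outputs are left to a separate shell document that is not available here, and a table limited to SC subjects would be compatible with the protocol's heading. The frequency tables might even count features such as erythema or pruritus among reported reactions, where IV placebo subjects would play no part. It stands that the shells could already avoid the problem. But the only rule that the SAP states is pooling without exception, and the qualifier about appropriateness decides whether a table is produced, not who is in it.

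The consequence is also limited. The summary is descriptive and the study is not powered for hypothesis tests. ISRs are listed by subject. The bias makes the drug look worse, so it cannot hide a signal. The pauses in Protocol 7.4.1 depend on events in LY3475766-treated subjects, not on a placebo percentage. All of this stands and keeps the point modest, although the printed percentage would still mislead.

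An SC-only placebo column would still mix subjects given 1, 3 and 6 injections. That is true: the change removes the mixing of routes but does not match each dose on number of injections.

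A reader might infer that infusion reactions in the IV cohorts are diluted in the same way. The SAP plans no infusion-reaction table, and Protocol 7.4.2.2 deals only with management, so the documents do not support a parallel finding. A reader might also take the three-reaction row above (25% against 50%) as the expected size. It rests on a placebo ISR rate for which the documents give no basis.

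**Conclusion.** The point holds as a defect in a stated rule with a modest consequence. As the SAP is written, the placebo ISR percentage includes IV placebo subjects who had no SC injection, and it is understated whenever at least one placebo ISR occurs. With none, both denominators give 0%.

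The printed rate is 0.50 of the SC-only rate for the planned 48 and about 0.57 with a full repeat of Cohort 4. Both figures assume cohorts of 8 (6 + 2), and the second also assumes that the repeat has 8 subjects and that all dosed subjects are counted. It would go too far to say that the rate is halved in every case, since the Safety population counts everyone dosed and up to 70 may be enrolled. No test, sample size or escalation rule changes. The conclusion also assumes that the unseen table shells follow the SAP text.

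**What to change.** In SAP 9.5.8, state that ISR summaries include only subjects dosed SC and that the placebo column is SC placebo (planned n = 6). Show the denominator in the column header, so that a Cohort 4 repeat or any replacements are visible.

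Because ISRs are also recorded as ordinary adverse events, the same dilution would remain in the frequency table of SAP 9.5.1. Keep pooled placebo there, and add a footnote giving the SC placebo denominator for ISR preferred terms, so that two different placebo percentages in the report can be reconciled.

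The cost is a sentence in the SAP, one table shell and one footnote. The drawback is a smaller placebo denominator and so a less precise placebo percentage. No new analysis of infusion reactions is needed for this point.
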